# The HAC Trial (Harmonic for Acute Cholecystitis) Study. Randomized, double-blind, controlled trial of Harmonic(H) versus Monopolar Diathermy (M) for laparoscopic cholecystectomy (LC) for acute cholecystitis (AC) in adults

**DOI:** 10.1186/1745-6215-10-34

**Published:** 2009-05-26

## Abstract

**Background:**

In the developmental stage of laparoscopic cholecystectomy (LC) it was considered 'unsafe' or 'technically difficult' to perform laparoscopic cholecystectomy for acute cholecystitis (AC). With increasing experience in laparoscopic surgery, a number of centers have reported on the use of laparoscopic cholecystectomy for acute cholecystitis, suggesting that it is technically feasible but at the expense of a high conversion rate, which can be up to 35 per cent and common bile duct lesions.

The HARMONIC SCALPEL(R) (H) is the leading ultrasonic cutting and coagulating surgical device, offering surgeons important benefits including: minimal lateral thermal tissue damage, minimal charring and desiccation.

Harmonic Scalpel technology reduces the need for ligatures with simultaneous cutting and coagulation: moreover there is not electricity to or through the patient Harmonic Scalpel has a greater precision near vital structures and it produces minimal smoke with improved visibility in the surgical field.

In retrospective series LC performed with H was demonstrated feasible and effective with minimal operating time and blood loss: it was reported also a low conversion rate (3.9%).

However there are not prospective randomized controlled trials showing the advantages of H compared to MD (the commonly used electrical scalpel) in LC.

**Methods/Design:**

Aim of this RCT is to demonstrate that H can decrease the conversion rate compared to MD in LC for AC, without a significant increase of morbidity.

The patients will be allocated in two groups: in the first group the patient will be submitted to early LC within 72 hours after the diagnosis with H while in the second group will be submitted to early LC within 72 hours with MD.

**Trial Registration:**

ClinicalTrials.gov Identifier: NCT00746850

## Background

In the developmental stage of laparoscopic cholecystectomy it was considered 'unsafe' or 'technically difficult' to perform laparoscopic cholecystectomy for acute cholecystitis [1,2].

With increasing experience in laparoscopic surgery, a number of centers have reported on the use of laparoscopic cholecystectomy for acute cholecystitis, suggesting that it is technically feasible but at the expense of a high conversion rate, which can be up to 35 per cent [3,4] and common bile duct lesions [5].

The HARMONIC SCALPEL^® ^(H) is the leading ultrasonic cutting and coagulating surgical device, offering surgeons important benefits including: minimal lateral thermal tissue damage, minimal charring and desiccation.

H technology reduces the need for ligatures with simultaneous cutting and coagulation: moreover there is not electricity to or through the patient

H has a greater precision near vital structures and it produces minimal smoke with improved visibility in the surgical field. [6]

In retrospective series LC performed with H was demonstrated feasible and effective with minimal operating time and blood loss: it was reported also a low conversion rate (3.9%). [6]

However there are not prospective randomized controlled trials showing the advantages of H compared to Monopolar Diathermy (MD – the most commonly used electrical scalpel) in LC.

Aim of this RCT is to demonstrate that H can decrease conversion rate compared to MD in LC for AC, without a significant increase of morbidity.

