### Statistical Methods and Power Calculations

By using StatCal of Epi INFO 2000 software package (Centers for Disease Control and Prevention, Atlanta, GA, USA), a sample size of 21 patients for each group (42 patients for the whole study) has been calculated to reach a confidence level of 95% with a power of 80%, supposing that the hospital stay for LC with H the conversion rate can be reduced from 35% to 3%.

Analysis of data is by intention-to-treat. It will be specified when and how any deviations from randomised allocation, false inclusions, or missing outcomes have been handled. Repeated measures of the outcome will be performed with complete case analyses, potentially excluding individuals with some follow-up data, Eventual missing outcomes will be imputed using baseline values or by assuming that all missing participants have the same risk as the observed participants in the control group.

Data are expressed as numbers (%) and means (SD). The results of the two groups in comparison are analyzed using the Pearson's chi-square test and Fisher exact test, as appropriate, for proportions in case of discrete data. Fisher exact test is used when the data are very unequally distributed among the cells of the table or the expected frequency of any cell is less than 5 or the total N is less than 50. For means in case of continuous numerical data, the independent samples T test and the Mann-Whitney U-test are used, respectively for data normally and non-normally distributed. The data are previously tested for normality by the Kolmogorov-Smirnov test. For multivariate analysis the stepwise logistic regression is applied. A *p*-value of < 0.005 is in any case considered to be statistically significant.

Forward selection has been used as variable selection method; it will include all the baseline variables and all baseline variables are assessed for imbalance. The final model only contain variables with a p-value less than 0.05. Imbalances of baseline variables are defined comparing the groups using t tests for continuous variables and χ^2 ^tests for categorical variables. The adjustments are based upon the stratified logrank test or analysis of covariance. [11-13]The primary outcome is the conversion rate. Secondary outcomes are: intra-operative and post-operative morbidity and mortality, operative time and intra-operative blood losses.

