There will be not inconveniences caused to the patients. No incentives are planned for the patients regarding the operation or the follow-up.

All the medical informations obtained from the patients will be kept confidentially among the research scientists conducting the study.

The patients will be free to withdraw from the study, whenever they want without any obligation.

The study will be stopped in case of newly discovered statistically significant advantages in one group.

The aim of the study is to demonstrate that H can reduce conversion rate compared to MD in LC for AC but also differences in terms of morbidity, mortality, operation time, hospital stay, postoperative pain, return to normal activity will be evaluated.

The primary endpoints of our study will be:

**A) **To evaluate the conversion rate

**B) **To evaluate morbidity, mortality, operation time

**C) **To evaluate hospital stay, postoperative pain, return to normal activity

The onset of any other complications will be recorded intraoperatively, postoperatively, at discharge, at 7-days, 1-month and 6-months.

The side effects that could have observed are not substantially different between the arms of the study.

All the above mentioned data will be recorded in the Case Report Form and later stored in computer database. At the end of the study the final statistical examination will be carried out.

An interim statistical examination of the data will be done every 3 months during the period of patients' inclusion in the study. Then at the end of every completed follow-up period (1-month, 6-months).

The statistical analysis will be carried out using Epi Info 2000, Version 1.1 software package (Dean AG, Arner TG, Sangam S, Sunki GG, Friedman R, Lantinga M, Zubieta JC, Sullivan KM, Smith DC. Epi Info 2000, a database and statistics program for public health professionals for use on Windows 95, 98, NT, and 2000 computers; Centers for Disease Control and Prevention, Atlanta, Georgia, USA, 2000)

No incentives are planned for the patients regarding the operation or the follow-up.

The study will take approximately 6 months – 1 year for the inclusion period. According to the number of AC managed monthly, the duration of the inclusion period can be approximately of 1 year to reach the number of about 42 enrolled patients.

An interim report is planned at the end of any completed follow-up period.

The trial has been registered with the ClinicalTrials.gov Identifier: NCT00746850 .

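### The morbidity half of the aim rests on a non-significant test in 21 versus 21 patients, which cannot support a conclusion on safety

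*Protocol article*

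**What the plan says.** The aim appears twice, in the Background and in the abstract under Methods/Design. Each time, what the trial is meant to demonstrate has two parts. The Background's version is that "H can decrease conversion rate compared to MD in LC for AC, without a significant increase of morbidity". The abstract's version is that "H can decrease the conversion rate compared to MD in LC for AC, without a significant increase of morbidity".

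Statistical Methods and Power Calculations fixes how this would be judged:

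- **Size.** It gives "a sample size of 21 patients for each group (42 patients for the whole study"), chosen "to reach a confidence level of 95% with a power of 80" per cent, on the supposition that "the conversion rate can be reduced from 35% to 3" per cent. Morbidity plays no part in this calculation.
- **Test.** Proportions are compared by Pearson's chi-square or Fisher's exact test. Fisher's is used when, among other conditions, "the expected frequency of any cell is less than 5 or the total N is less than 50". With 42 patients, Fisher's test applies.
- **Threshold.** A p-"value of < 0.005 is in any case considered to be statistically significant".
- **Status.** Morbidity is a secondary outcome in this section, but stands under the primary endpoints in Data Collection.

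Data Collection also contains this sentence: "The side effects that could have observed are not substantially different between the arms of the study".

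**The concern.** An ordinary difference test asks whether there is enough evidence to declare a difference. When it does not reject, the data may show similar rates or may simply be too few. The aim makes no such distinction. It places the absence of a significant increase inside what is to be demonstrated, and the article offers no other yardstick for that half, such as a margin or a rule based on a confidence interval. The smaller the trial and the stricter the threshold, the easier this half of the aim is to meet.

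Morbidity is a real question here. Under Intervention, the cystic artery and duct are clipped in the MD group and closed by the device itself in the H group. Data Collection lists bile duct injury and hemorrhage among the complications to be classified. A true increase could sit behind a statement that morbidity did not rise significantly, and readers would take that statement as half of the trial's positive result.

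**Working it through.** **Inputs from the article.** 21 per arm; conversion 35% versus 3%; 95% confidence, 80% power; Fisher's exact test; threshold 0.005.

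**Assumptions.** Two-sided testing, since sidedness is not stated. MD morbidity of 5% to 20%, with 30% as a further check, since no rate is given. Because 0.005 disagrees with the 95% confidence used for sizing, every result is shown at both 0.05 and 0.005.

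**Step 1: reproduce the stated sample size.**

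Unpooled: n = (1.96 + 0.8416)² × (0.35×0.65 + 0.03×0.97) / 0.32² = 7.849 × 0.2566 / 0.1024 = 19.7, so 20 per arm.

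Pooled, mean rate 0.19: n = [1.96√(2×0.19×0.81) + 0.8416√0.2566]² / 0.1024 = 22.4, so 23 per arm.

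The stated 21 lies between these. It is a size for a drop of 32 percentage points in conversion and for nothing else.

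**Step 2: what the morbidity test can detect at 21 versus 21.** The power is the sum, over all pairs (i, j) of event counts under MD and H with j > i and two-sided Fisher p below the threshold, of Bin(i; 21, p_MD) × Bin(j; 21, p_H).

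| True rates, MD to H | Detected, p < 0.05 | Missed | Detected, p < 0.005 | Missed |
|---|---|---|---|---|
| 5% to 10% | 1.9% | 98.1% | 0.02% | 99.98% |
| 10% to 20% | 7.8% | 92.2% | 0.6% | 99.4% |
| 15% to 30% | 13.1% | 86.9% | 2.0% | 98.0% |
| 20% to 40% | 19.1% | 80.9% | 4.1% | 95.9% |
| 30% to 60% | 36.0% | 64.0% | 14.9% | 85.1% |

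**Step 3: counts needed for significance.**

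| MD events of 21 | H events needed, p < 0.05 | H events needed, p < 0.005 |
|---|---|---|
| 0 | 5 | 8 |
| 1 | 7 | 10 |
| 2 | 9 | 12 |

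Hand check of the first row: for k versus 0 events, p = 2 × C(21,k) / C(42,k). For k = 5 this is 2 × 20,349 / 850,668 = 0.048. For k = 7 it is 0.0086 and for k = 8 it is 0.0034. So 7 complications against none would not be significant at 0.005.

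Observed doublings are also far from significant: 2 versus 4 gives p = 0.66, 3 versus 6 gives 0.45, 4 versus 8 gives 0.31, and 5 versus 10 gives 0.20.

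**Step 4: precision.** With equal true rates p, the 95% half-width for the risk difference is 1.96√(2p(1−p)/21). At p = 0.10 this is 1.96√(0.18/21) = 0.181. At p = 0.20 it is 1.96√(0.32/21) = 0.242. With 3 events in each arm, the Newcombe 95% interval runs from about −22 to +22 percentage points. With no events in 21, the upper 97.5% limit for that arm is 1 − 0.025^(1/21) = 16%.

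**Step 5: what a real safety claim would need.** For 80% power to detect a doubling at two-sided 0.05, 435, 199, 121 and 82 patients per arm are needed at MD rates of 5%, 10%, 15% and 20%. For non-inferiority with a purely illustrative 10-point margin, one-sided 0.025 and equal rates of 10%, n = 7.849 × 0.18 / 0.10² = 141.3, so 142 per arm. At 20% it is 252.

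**The case against.** The strongest reply is that the article nowhere says a non-significant p-value will be taken as proof of no increase. The phrase is one clause of a condensed article. The statistical section names conversion as the primary outcome, and margins or power for secondary safety outcomes are often left to other documents. This stands in part: their absence is not itself a fault. What remains is the wording the article does contain. The clause is part of what is to be demonstrated, and the only criterion supplied for it is a difference test.

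A second reply is that the size depends on an assumed morbidity rate and partly on the 0.005 threshold, which may be a slip. Both are true. The complications listed are broad, so the rate could be higher, and at 30% to 60% detection at 0.05 rises to 36%. The conclusion nevertheless holds at 0.05 across the assumed range. The conflict over the threshold is a separate matter.

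A third reply is that harm would not be hidden. Data are to be given as numbers and percentages, complications are classified by type, and they are recorded to 6 months. This also stands: the counts should be visible. The fault is in the conclusion the aim allows to be drawn from them.

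Two stronger readings are tempting. A reader might infer that the safety conclusion is guaranteed whatever the data. It is not, since 8 versus 0 or 10 versus 1 would overturn it even at 0.005. A reader might also infer that the side-effects sentence asserts as established fact that the arms do not differ. The sentence is garbled and can equally be read as an expectation of comparable risk, so the documents do not secure that charge.

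**Conclusion.** The point holds as a fault in a stated criterion. The safety half of the aim can be met by failing to reject in a trial sized only on conversion. For assumed MD morbidity of 5% to 20%, a true doubling under H would be missed in about 81% to 98% of trials at p < 0.05 and in about 96% or more at p < 0.005. These are probabilities resting on assumed rates, two-sided testing and 21 analysed patients per arm; they do not say that the trial must reach a reassuring result. The primary comparison of conversion rates is not affected. What changes is what the trial may conclude about morbidity. The aim should be corrected, because half of it cannot be supported as written.

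**What to change.** - In the Background and the abstract, limit the confirmatory aim to the conversion rate.
- Report morbidity by arm as counts and as a risk difference with a 95% confidence interval.
- State that a non-significant p-value will not be interpreted as absence of increased morbidity, and that a trial of this size cannot exclude a clinically important increase. Any figure given should be marked as illustration only: the half-width is about 18 to 24 points under assumed rates of 10% to 20%.
- Under Data Collection, reword the side-effects sentence as an expectation, since morbidity is an outcome under evaluation.

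The cost is wording and one interval estimate, with no extra patients or data. The downside is a more modest safety claim. Keeping a confirmatory safety claim would instead require a justified margin and a far larger trial, such as the 142 per arm shown above for one illustrative case.

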## Methods

The study project is a prospective, randomized investigation. The study will be performed in the Department of Emergency Surgery St Orsola-Malpighi University Hospital (Bologna, Italy), a large teaching institutions, with the participation of all surgeons who accept to be involved in.

The Ethic Committee of St. Orsola Malpighi University Hospital has approved the study protocol on June 24^th ^2008. The study and its Informed Consent form have been judged by the Committee to be ethically and scientifically satisfactory as well as correct and adequate to the aims.

The patients will be allocated in two groups: in the first group the patient will be submitted to early LC within 72 hours after the diagnosis with H while in the second group will be submitted to early LC within 72 hours with MD.

The randomization will be obtained through computer-generated schedule. Blocked randomization is used to ensure close balance of the numbers in each group at any time during the study. The result of this randomization will be sealed in numbered envelopes, inserting inside a cardboard to ensure that they are opaque. After cholecystitis diagnosis if the patient fulfils the inclusion criteria the responsible surgeon will ask the patient to partecipate to the study. If the patient agree, he/she will sign the informed consent. After patient's consent the randomization will be carried out. The responsible surgeon will record the patient name (and number). [7-9]

All eligible patients will be recorded. [10]

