### Intervention

Preoperative data collected will include patient demographics and comorbidity conditions (genitourinary, cardiac, pulmonary, gastrointestinal, renal, or rheumatologic) and a detailed history of symptom onset.

The procedure was performed by a surgeon that had performed at least 50 LCs.

On admission, the patients were started on cefotaxime, 2 g IV every 12 h, which was continued postoperatively according to NNISS score.

The standard four-trocar operative technique is used for LC for acute cholecystitis.

When the gallbladder is distended it will be first aspirated. To allow a good hold on the gallbladder larger graspers will be inserted through a 5 mm right lower port. The cystic artery and duct are clip-ligated in the MD group whereas in the H group cystic artery and duct are closed by H. In the H group the surgeon will use only H, whereas in the MD group the surgeon will use only MD. The gallbladder and intraperitoneal "dropped" stones are collected in an endoscopic bag and extracted through the umbilical cannula site, which can be extended. A closed system suction drain is left. Fascial closure is attempted only at the umbilical cannula site. The skin at all the cannula sites are closed with staples. Conversion to laparotomy will be decided by the operating surgeon and each conversion will be motivated.

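### Randomisation follows consent, and no stated rule fixes the operator or operating slot first, so either could be chosen with the arm known and could confound instrument with operator

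*Protocol article*

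**What the plan says.** All references are to the protocol article.

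- **Sequence (Methods).** Recruitment starts at diagnosis: "After cholecystitis diagnosis if the patient fulfils the inclusion criteria the responsible surgeon will ask the patient to partecipate to the study". Then, once consent is given: "the randomization will be carried out. The responsible surgeon will record the patient name (and number". Allocation is tied to consent and not to arrival in theatre or the start of the operation.
- **Interval (Methods).** For the Harmonic (H) arm: "in the first group the patient will be submitted to early LC within 72 hours after the diagnosis with H". The monopolar diathermy (MD) arm has the same 72 h limit.
- **Concealment (Methods).** "The result of this randomization will be sealed in numbered envelopes, inserting inside a cardboard to ensure that they are opaque". Blocking is described as a means of balancing group numbers.
- **Operators (Methods, Intervention).** The study runs in one department, "with the participation of all surgeons who accept to be involved in". The one stated requirement is: "The procedure was performed by a surgeon that had performed at least 50 LCs".
- **Primary outcome (Intervention; Statistical Methods and Power Calculations).** This is conversion, and the operating surgeon decides it.
- **Imbalance control (Statistical Methods and Power Calculations).** The factors named are patient characteristics. Operator and time to surgery are not among them.
- **Blinding (Data Collection).** The team described as unaware of the instrument takes over after the operation.

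**The concern.** Randomisation balances what exists when the envelope is opened. It does not balance what is decided afterwards. Here two influences on conversion, operative time and blood loss may still be undecided at that moment: who operates, and when.

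The 50-LC threshold does not distinguish instruments. The Background describes MD as the electrical instrument in most common use, and the Intervention section has the cystic artery and duct closed by H in one arm and clipped in the other. A surgeon can therefore qualify for the H arm with no H cases. Conversely, directing H patients to a colleague practised with H, while MD patients go to whoever is on duty, would breach nothing written. A patient may also withdraw or be postponed in the interval with the arm already known.

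If operator or slot did follow the arm, the trial would compare H with its chosen operator against MD with another. A lower conversion rate could then not be credited to the instrument.

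**Working it through.** **1. The plan's own figures.** Statistical Methods and Power Calculations gives 21 per group for 35% v 3% conversion, 95% confidence and 80% power. With unpooled variance, n = (1.960 + 0.842)² × (0.35 × 0.65 + 0.03 × 0.97) / 0.32² = 7.85 × 0.2566 / 0.1024 = 19.7, so 20. The pooled-variance form gives 23. The stated 21 lies between them, so I take a two-sided 0.05 test as its basis. The same section elsewhere sets significance at p < 0.005, so both thresholds are carried below.

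**2. Events available for adjustment.** Expected conversions are 0.35 × 21 = 7.35 (MD) and 0.03 × 21 = 0.63 (H), together 7.98, or about 8. That is too few to separate an operator effect from an instrument effect by regression if operator tracks arm.

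**3. Stated safeguards against the gap.**
- Opaque envelopes protect enrolment, not decisions taken after opening.
- Blocking balances numbers, not operators.
- The named imbalance factors describe patients.
- The blinded team acts after the primary outcome has been determined.
- Intention-to-treat analysis keeps patients in their arm but does not equalise who operated on them.

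None of these fixes operator or slot before the arm is known.

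**4. Illustration of size.** Assumptions that are not in the documents: the instrument has no effect; experienced operators convert 10% and others 35%; f is the share of an arm's operations done by experienced operators. The arm's conversion rate is

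p = 0.10 f + 0.35 (1 − f).

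Equal mix (f = 0.5 in both arms): p = 0.05 + 0.175 = 0.225 in both.
80/20 v 20/80: H = 0.08 + 0.07 = 0.15; MD = 0.02 + 0.28 = 0.30; spurious difference 15 points.

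The rejection probability is the sum, over all pairs of binomial counts with 21 per arm, of their joint probability where the two-sided Fisher p falls below the threshold.

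| Experienced share, H v MD | H rate | MD rate | P(p < 0.05) | P(p < 0.005) |
|---|---|---|---|---|
| 50% v 50% | 22.5% | 22.5% | 2.3% | 0.1% |
| 70% v 30% | 17.5% | 27.5% | 6.7% | 0.8% |
| 80% v 20% | 15% | 30% | 13.2% | 2.0% |
| 100% v 0% | 10% | 35% | 38.3% | 10.4% |

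**5. Range.** If experienced operators convert 15% or 5% instead of 10%, the 80/20 v 20/80 case gives a spurious difference of 12 or 18 points. The chance of p < 0.05 is then 8.4% or 20.6%, and of p < 0.005 it is 1.1% or 3.6%.

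**The case against.** The strongest reply is that much of this rests on silence. The article does not say when the operator is assigned. A rota may settle it, or the surgeon who recruits may also operate. It is a condensed article, and theatre logistics are commonly left to the full protocol. Randomising after consent is ordinary practice, 72 h is a ceiling in an emergency department and not the usual gap, and concealment before enrolment is properly described. Deviations are to be reported and each conversion justified.

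Most of this stands, and it limits what can be said. A reader might infer that allocation is known before any operator is fixed, that the responsible surgeon opens the envelope, or that instrument and operator are in fact confounded. The documents support none of these. They say that this surgeon seeks consent and records the patient, not who opens the envelope or how operators are chosen.

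A reader might also argue from fragility. At 21 per arm, 1 v 7 conversions gives Fisher p = 0.045, but 2 v 7 gives 0.130 and 1 v 6 gives 0.093, so one operator-driven conversion would reverse the result. That shows only that the trial is small: a one-patient change from any cause does the same. None of the three tables reaches the stated p < 0.005.

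What the objection does not remove is the stated sequence. The article itself ties allocation to consent and allows an interval before surgery, and a later analysis plan cannot alter when an envelope was opened.

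**Conclusion.** The point holds as a risk. As written, the plan permits operator or timing to be chosen with the arm known, and permits dropout with the arm known. Either could bias the comparison, and the surgeon who determines the primary outcome is not blinded.

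The size depends on how unevenly operators are used and how much they differ, and the documents give neither. Under the assumed 10% and 35% rates, an 80/20 v 20/80 mix raises the false-positive chance from 2.3% to 13.2% at 0.05, and from 0.1% to 2.0% at 0.005. A milder 70/30 v 30/70 mix gives 6.7% and 0.8%. With about 8 events, later adjustment would not be reliable. Prevention is cheap, so the change should be made, although nothing shows that the bias occurs.

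**What to change.** In Methods, keep consent at diagnosis but open the sealed envelope only in theatre, immediately before the operation. Before it is opened, the name of the operating surgeon and his or her previous LC counts with H and with MD are written on the outside. Operator and slot are then settled before the arm is known. Report operator, operator experience and time to surgery by arm.

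The cost is a change of wording and a few items to record; the sample size is unaffected. Both instruments must be available for every consented patient, and consented patients who never reach theatre are logged but not randomised. The change does not remove the operator's unblinded decision to convert.
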